## Changes in Version 2.5 (Feb 2016) compared to Version 2.4.2 (Oct 2014) of the research protocol

- changes in the text are marked in red -

Page 12: Since the overall sample size needed to be increased, we adapted both the number of centers and the number of patients per center to be randomized. We now expect to have 90 centers (instead of 60), each randomizing at least 24 (instead of 12 to 13) eligible patients.

Page 13: Sample size was re-calculated as newly described. The original description of the methods was kept in place and slightly modified. The following text was added: *[Accordingly, the previous Sample size was re-estimated based on recommendations of the DSMB after data on the first 618 patients revealed that the incidence of the collapsed composite outcome was considerably lower than expected. In the revised calculations, the control group incidence was assumed to be 0.20 (instead of 0.40), and sample size was calculated to have 80% power at the overall 0.05 significance level to detect a relative risk (as originally planned) of 0.75. This design requires a maximum of 1912 patients, adjusting for the interim monitoring for efficacy and futility as described in section 8.2. Assuming a dropout rate of 5%, a total of 2013 patients need to be included into the study. East 6.0 interim monitoring software (Cytel, Cambridge, MA, USA) was used.]*

Page 23: Interim analyses were planned. The following text, including one table and one figure was added: *[Interim analyses for efficacy and futility will be conducted at 50% (N=956), 75% (N=1434) and 100% (N=1912) of the planned enrollment, as needed, using a non-binding group sequential design with gamma spending functions ( $\gamma = -4$  for each of  $\alpha$  and  $\beta$ ). The table below shows the  $\alpha$  and  $\beta$  spent over the trial, z-statistic boundaries for efficacy and futility, and boundary crossing probabilities under the alternative hypothesis ( $H_1$ ). The corresponding P-value boundaries for efficacy (futility in parentheses) at the 1st, 2nd and final looks, respectively, are  $P \leq 0.006$  ( $P > 0.82$ ),  $P \leq 0.015$  ( $P > 0.35$ ) and  $P \leq 0.044$  ( $P > 0.044$ ). The Figure below displays the z-statistic boundaries for efficacy/harm and futility as a function of accrued sample size.]*

Page 25: Prof. [name], University Hospital of Bonn, Germany joined the Data Safety and Monitoring Board (DSMB). Now, the DSMB is composed of 5 individuals.

## Changes in Version 2.4.2 (Oct 2014) compared to Version 2.4.1 (Jun 2013) of the research protocol

Page 12: *Section 6.5 [Interim Analyses: Planned interim analyses will be performed after 50% of the patients required (n=374 patients) have been randomized and treated in the study. Early termination of the study may be considered if very strong differences between the two treatment groups become apparent. Very strong differences are defined as risk ratio smaller than 0.5 (e.g. event rate in higher PEEP group < 20%, event rate in lower PEEP group 40%) or greater than 2.0 (e.g. event rate in higher PEEP group > 80%, event rate in lower PEEP group 40%). The decision to terminate the study early will be made by a data and safety monitoring board (DSMB). Except in the case of early study termination, the results of the interim analysis will not be disclosed to the participating study centers.] is deleted. There will be no interim analyses during the study.*

Page 22: *The statistical analysis section (8.2) is actualized and extended. The primary endpoint and its analysis plan were clearly defined.*

Page 23: *Details on how to report Adverse Events (AE) are added by using the new Appendix v. (page 34-35)*

Page 23: *[Prof. [name], University of Münster, Germany] deleted. Since he is not a member, at present, the DSMB is composed of four individuals.*

Page 33: *The study sheet (Appendix iv) was overall actualized. Mainly, patient visits on postoperative days 2 and 4 are added. These additional visits were already described in the text (page 19) in the former versions of the protocol (2.4 and 2.4.1).*

## Changes in Version 2.4.1 (Jun 2014) compared to Version 2.4 (Nov 2013) of the research protocol of

### Protective Ventilation with Higher versus Lower PEEP during General Anesthesia for Surgery in OBESE Patients – The PROBESE Randomized Controlled Trial

Page 1: [name], Sheffield Teaching Hospitals, United Kingdom, Operating Services, Critical Care and Anaesthesia (OSCCA) *added to the steering committee*

Page 6: [While anesthesiologists tend to use PEEP higher than in non-obese patients] *deleted*

Page 11: *Inclusion criteria* [Patient scheduled for open or laparoscopic surgery under general anesthesia] *changed to* [Patient scheduled for surgery under general anesthesia]

Page 32: *Definition of Hepatic failure:* [Serum bilirubin level > 2 mg/dL with elevation of the transaminase and lactic dehydrogenase levels above twice normal values] *changed to* [Hepatic failure during short term follow up (5 postoperative days) is considered as follows: Ratio of total bilirubin on postoperative day 5 to postoperative day 1 > 1,7 and ratio of international normalized ratio (INR) on postoperative day 5 to postoperative day 1 >1,0; during long term follow up (until postoperative day 90) at new presence of hepatic encephalopathy and coagulopathy (INR > 1,5) within 8 weeks after initial signs of liver injury (e.g. jaundice) without evidence for chronic liver disease]

## 1. LIST OF ABBREVIATIONS AND RELEVANT DEFINITIONS

|      |                                           |
|------|-------------------------------------------|
| AE   | Adverse Event                             |
| ALI  | Acute Lung Injury                         |
| AR   | Adverse Reaction                          |
| ARDS | Acute Respiratory Distress Syndrome       |
| BMI  | Body Mass Index                           |
| CA   | Competent Authority                       |
| COPD | Chronic Obstructive Pulmonary Disease     |
| CPAP | Continuous Positive Airway Pressure       |
| EU   | European Union                            |
| ICU  | Intensive Care Unit                       |
| NPPV | Noninvasive Positive Pressure Ventilation |
| OSA  | Obstructive Sleep Apnea                   |
| PEEP | Positive end–expiratory pressure          |
| PPC  | Postoperative Pulmonary Complication      |
| VALI | Ventilator–associated lung injury         |

## 2. SUMMARY

### Rationale

Postoperative respiratory failure, particularly after surgery under general anesthesia, adds to the morbidity and mortality of surgical patients. Anesthesiologists inconsistently use positive end-expiratory pressure (PEEP) and recruitment maneuvers in the hope that this may improve oxygenation and protect against postoperative pulmonary complications (PPCs), especially in obese patients. While it is uncertain whether a strategy that uses higher levels of PEEP with recruitment maneuvers truly prevents PPCs in these patients, use of higher levels of PEEP with recruitment maneuvers could compromise intra-operative hemodynamics.

### Objectives

To compare a ventilation strategy using higher levels of PEEP with recruitment maneuvers with one using lower levels of PEEP without recruitment maneuvers in obese patients at an intermediate-to-high risk for PPCs.

### Hypotheses

An intra-operative ventilation strategy using higher levels of PEEP and recruitment maneuvers, as compared to ventilation with lower levels of PEEP without recruitment maneuvers, prevents PPCs in obese patients at an intermediate-to-high risk for PPC.

### Study design

International multicenter randomized controlled trial.

### Study population

Obese patients with BMI  $\geq 35$  kg/m^2 at intermediate-to-high risk for PPCs scheduled for surgery under general anesthesia.

### Main study parameters/endpoints

The primary endpoint is the proportion of patients with PPCs. Secondary endpoints include intra-operative complications, need for postoperative ventilatory support (invasive and/or non-invasive ventilation), need for unexpected ICU admission or ICU readmission, the number of hospital-free days and 90-day survival/mortality.

### Nature and extent of the burden and risks associated with participation, benefit and group relatedness

In the intra-operative period, patients will not experience discomfort from either strategy because of general anesthesia. However, systemic hypotension could occur in the higher PEEP group, which would be treated with intravascular volume therapy and/or vasoactive drugs. If the hypothesis proves to be true, patients in the higher PEEP group could benefit from a lower incidence of PPCs. Blood samples will be collected via an existing intravenous catheter or via direct vein puncture, but always in combination with blood sampling for routine care; the amount of additional blood samples can be considered minimal.

### 3. INTRODUCTION AND RATIONALE

#### 3.1 Postoperative pulmonary complications

Postoperative pulmonary complications, especially postoperative respiratory failure, add to the morbidity and mortality of surgical patients. An ARISCAT score  $\geq 26$  is associated with an intermediate-to-high risk of postoperative pulmonary complications (PPCs), independent of BMI.

#### 3.2 Ventilator-associated lung injury

Even though mechanical ventilation is a life-saving strategy in patients with respiratory failure and frequently necessary during general anesthesia, both experimental and clinical studies show that mechanical ventilation has the potential to aggravate or even initiate lung injury (so-called ventilator-associated lung injury, VALI). Repetitive collapse/reopening of lung units (atelectrauma) and overdistension of lung units (volutrauma) are possible mechanisms underlying VALI. While positive end-expiratory pressure (PEEP) can minimize atelectrauma, lower tidal volumes are thought to reduce volutrauma. One meta-analysis showed that use of lower tidal volumes is associated with a better outcome for patients with uninjured lungs. This study included both surgery patients who underwent mechanical ventilation for general anesthesia as well as critically ill patients who required longer mechanical ventilation. Notably, a more recent meta-analysis showed a decrease in lung injury development, pulmonary infection and atelectasis in patients receiving intraoperative mechanical ventilation with both lower tidal volumes and higher levels of PEEP.

#### 3.3 Postoperative pulmonary complications and mechanical ventilation

Mechanical ventilation is frequently required in patients undergoing surgery. Our group has shown that an intraoperative ventilation strategy with lower tidal volume and positive end-expiratory pressure (PEEP) may improve postoperative lung function and even outcome in patients undergoing open abdominal surgery. More recently, a similar mechanical ventilation strategy was shown to reduce the incidence of PPCs and health care utilization in intermediate-to-high risk patients with a body mass index (BMI)  $< 35 \text{ kg/m}^2$  undergoing open abdominal surgery. A recently concluded multicenter, international, randomized controlled trial could not show a protective effect of higher PEEP and recruitment against PPCs in patients with a BMI  $< 40 \text{ kg/m}^2$ . However, most of the patients included were not obese, i.e. had a BMI  $< 30 \text{ kg/m}^2$ . Therefore, these results cannot be extrapolated to obese patients.

#### 3.4 Mechanical ventilation in obese patients

According to Pelosi and Gregoretti, body mass is an important determinant of respiratory function before and during anesthesia not only in morbidly, but also in moderately obese patients. The impairment can manifest as (a) reduced lung volume with increased atelectasis and/or small airway closure; (b) derangements in respiratory system, lung and chest wall

compliance and increased resistance; and (c) moderate to severe hypoxemia. These physiological alterations are more marked in obese patients with hypercapnia or obstructive sleep apnea syndrome. In order to avoid or reduce such complications, PEEP levels should, theoretically, be set higher in obese than in non-obese patients. However, there is as of yet no clinical evidence supporting such an approach. In fact, an observational study conducted in 28 centers in France revealed that most patients undergoing general surgery, including obese ones, were ventilated with low ( $\leq 4$  cmH2O) or even without PEEP, even though average PEEP was higher in obese compared to non-obese patients. While there is uncertainty about the lung protective effects of PEEP, there is considerable evidence that tidal volumes in the range of 6 to 8 ml/kg of predicted body weight (PBW) is protective also in non-injured lungs, independent of BMI.

## **4. OBJECTIVES AND HYPOTHESIS**

### **4.1 Objectives**

The proposed randomized controlled trial aims at comparing the effects of higher levels of PEEP with recruitment maneuvers versus lower levels of PEEP without recruitment maneuvers on pulmonary and extra-pulmonary outcome measures during general anesthesia for surgery, as well as determining the length of hospital stay for obese patients at intermediate-to-high risk for PPCs and undergoing mechanical ventilation with lower tidal volumes.

### **4.2 Hypothesis**

We hypothesize that an intra-operative ventilation strategy using higher levels of PEEP and recruitment maneuvers, as compared to ventilation with lower levels of PEEP without recruitment maneuvers, prevents PPCs in obese patients at a intermediate-to-high risk for PPCs.

## 5. STUDY DESIGN

Multicenter, international, randomized controlled trial on obese patients with BMI  $\geq 35$  kg/m^2 at intermediate-to-high risk for PPCs and scheduled for general anesthesia because of surgery.

## 6. STUDY POPULATION

### 6.1 Population (base)

We intend to recruit obese patients with BMI  $\geq 35$  kg/m^2 consecutively scheduled for surgery in the participating hospitals during a period of 2 years. Currently, we expect about 90 centers to participate in the trial. Surgical patients in these centers will be screened daily. Demographic data on screened patients, regardless of enrollment criteria match, will be recorded (registry). We will randomize 2013 patients admitted to the participating centers and expect each participating center to randomize at least 24 patients who meet all inclusion criteria.

### 6.2 Inclusion criteria

- Patient scheduled for surgery under general anesthesia
- Intermediate-to-high risk for PPCs following surgery, according to the ARISCAT risk score ( $\geq 26$ ) (see APPENDIX i)
- BMI  $\geq 35$  kg/m^2
- Expected duration of surgery  $\geq 2$  h

### 6.3 Exclusion criteria

- Age  $< 18$  years
- Previous lung surgery (any)
- Persistent hemodynamic instability, intractable shock (considered hemodynamically unsuitable for the study by the patient's managing physician)
- History of previous severe chronic obstructive pulmonary disease (COPD) (non-invasive ventilation and/or oxygen therapy at home, repeated systemic corticosteroid therapy for acute exacerbations of COPD)
- Recent immunosuppressive medication (patients receiving chemotherapy or radiation therapy up to two months prior to surgery)
- Severe cardiac disease (New York Heart Association class III or IV, acute coronary syndrome or persistent ventricular tachyarrhythmias)
- Invasive mechanical ventilation longer than 30 minutes (e.g., general anesthesia for surgery) within last 30 days
- Pregnancy (excluded by anamneses and/or laboratory analysis)
- Prevalent acute respiratory distress syndrome expected to require prolonged postoperative mechanical ventilation
- Severe pulmonary arterial hypertension, defined as systolic pulmonary artery pressure  $> 40$  mmHg
- Intracranial injury or tumor
- Neuromuscular disease (any)

- Need for intraoperative prone or lateral decubitus position
- Need for one-lung ventilation
- Cardiac surgery
- Neurosurgery
- Planned reintubation following surgery
- Enrolled in other interventional study or refusal of informed consent

#### 6.4 Sample size calculation

**Initial** sample size calculation was based on our primary hypothesis and primary study outcome, and was informed by data collected during a multicenter Spanish trial (ARISCAT) (see APPENDIX i) and a single-center, relatively small study reporting the effects of intraoperative higher PEEP and recruitment maneuvers on the incidence of postoperative desaturation, chest infection and bronchospasm in obese patients who underwent laparoscopic bariatric surgery.

These calculations indicated that 356 patients were required per group, assuming a two-sided significance level of 0.05 and a power of 80%, to detect the expected difference in postoperative pulmonary complications between the higher PEEP group of 30% and the lower PEEP group of 40% (risk ratio of 0.75). Assuming a dropout rate of 5%, **a total of 748 patients** (n=374 per group) were planned to be included into the study.

Sample size was re-estimated based on recommendations of the DSMB after data on the first 618 patients revealed that the incidence of the collapsed composite outcome was considerably lower than expected. In the revised calculations, the control group incidence was assumed to be 0.20 (instead of 0.40), and sample size was calculated to have 80% power at the overall 0.05 significance level to detect a relative risk (as originally planned) of 0.75. This design requires a maximum of 1912 patients, adjusting for the interim monitoring for efficacy and futility as described in section 8.2. Assuming a dropout rate of 5%, a total of 2013 patients need to be included into the study. East 6.0 interim monitoring software (Cytel, Cambridge, MA, USA) was used.

## 7. METHODS

### 7.1 Study parameters/endpoints

#### 7.1.1 Main study parameter/endpoint

- Postoperative pulmonary complications

#### 7.1.2 Secondary study parameters/endpoints

- Intra–operative complications, i.e., complications related to the ventilation strategy (for example: de–saturation, defined as  $\text{SpO}_2 \leq 92\%$ , for  $> 1$  min; hypotension during recruitment maneuvers, as defined by systolic arterial pressure  $< 90$  mmHg for  $> 2$  min)
- Need for postoperative ventilatory support (invasive or non–invasive ventilation)
- Unexpected need for ICU admission (i.e., before surgery the patient is not scheduled for ICU admission, but is admitted eventually) or ICU readmission within 30 days
- Need for hospital readmission within 30 days
- Hospital–free days at day 90
- Mortality at day 90
- Postoperative extra–pulmonary complications
- Postoperative wound healing 

#### 7.1.3 Other study parameters

- Systemic levels of markers of (pulmonary) inflammation
- Systemic levels of markers of lung injury
- Systemic levels of markers of distal organ injury

### 7.2 Study procedures

Surgical patients in participating centers will be considered eligible if they fulfill the entry criteria. Eligible patients will be screened, their demographic data recorded (registry: age, gender, type of surgery), and those without exclusion criteria will be randomized. In total, 748 patients will be included.

#### *Patient Consent*

All patients or legal guardians must provide written informed consent according to local regulations before inclusion in the study.

#### 7.2.1 Randomization

##### *Randomization procedure*

Randomization will be performed using a dedicated website and will be balanced per center. Randomization must take into account the risk of developing pulmonary complications (ARISCAT, see APPENDIX i.) to assure a balance for both intermediate and high–risk subgroups.

### *Randomization arms*

Central randomization with the use of a permuted-block randomization list (block length 6) will be used. Before surgery patients will be randomly assigned 1:1 to mechanical ventilation with PEEP of 4 cmH2O without recruitment maneuvers (the “lower PEEP level”) or mechanical ventilation with PEEP of 12 cmH2O with the use of recruitment maneuvers (the “higher PEEP level”). If desaturation, defined as SpO2 ≤ 92% for > 1 min, occurs, rescue is performed according to the sub-section “Rescue Therapy”. Both strategies were chosen taking into account a recent national survey in France, most recent randomized clinical trials on mechanical ventilation of obese patients undergoing surgery and expert consensus, which was obtained during a meeting of the Respiration Subcommittee at Euroanaesthesia 2013 in Barcelona, Spain.

At each site at least two investigators will be involved: one who will be aware of the allocated intervention and collect intra-operative data; the other who will remain blinded to the intra-operative interventions and evaluate the outcomes, scoring postoperative pulmonary and extrapulmonary complications.

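### A single disclosed block length of 6, with allocation open at each site, could let a site member who tracks allocations deduce about a fifth to a quarter of them, if blocks run within centre

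*Protocol*

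**What the plan says.** Section 7.2.1 of the protocol has two relevant parts.

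- **Randomization procedure.** "Randomization will be performed using a dedicated website and will be balanced per center". It adds: "Randomization must take into account the risk of developing pulmonary complications", so that the intermediate-risk and high-risk groups are both balanced.
- **Randomization arms.** "Central randomization with the use of a permuted-block randomization list (block length 6) will be used", with 1:1 assignment before surgery. Each site has at least two investigators: "one who will be aware of the allocated intervention and collect intra-operative data", and "the other who will remain blinded to the intra-operative interventions and evaluate the outcomes".

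Section 6.1 gives the scale: "Currently, we expect about 90 centers to participate in the trial", 2013 patients to be randomized, and at least 24 per centre.

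The protocol does not say whether a separate block list runs in each centre or in each centre-by-risk cell. It does not say who screens, seeks consent and enrols. It does not say whether that person is kept from knowing earlier allocations.

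**The concern.** Central web randomization hides the list. It does not hide what can be worked out from past assignments when the block length is known. The two ventilation strategies differ visibly in theatre (PEEP 4 without recruitment maneuvers against PEEP 12 with them), so past assignments are known to someone at the site. Once three patients in a block have gone to one arm, the rest of that block is fixed.

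Someone who knows the next assignment and also influences enrolment could defer a case or not approach a patient. Eligibility leaves room for this: expected duration of surgery and haemodynamic suitability are partly matters of judgement, and consent and randomization both precede surgery. Bias that enters at enrolment is not removed by blinded outcome scoring or by intention-to-treat analysis.

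**Working it through.** The protocol gives no figure for predictability, so there is none to reproduce.

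**Inputs.** Block length 6 and 1:1 allocation, so 3 + 3 per block (section 7.2.1). About 90 centres, 2013 patients and at least 24 per centre (section 6.1). The average is 2013/90 = 22.4 per centre, or 2013/180 = 11.2 per centre-by-risk stratum if the two risk classes were equally frequent. That equal split is an assumption, because the protocol gives none.

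**Step 1: one complete block.** There are C(6,3) = 20 equally likely orders. An allocation is certain when one arm already has its three patients. The best guess is the arm with more places left in the block.

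| Position | 1 | 2 | 3 | 4 | 5 | 6 |
|---|---|---|---|---|---|---|
| Chance already certain | 0 | 0 | 0 | 2/20 = 0.10 | 8/20 = 0.40 | 20/20 = 1.00 |
| Best-guess accuracy | 0.50 | 0.60 | 0.60 | 0.70 | 0.70 | 1.00 |

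- Certain: (0.10 + 0.40 + 1.00)/6 = 1.5/6 = 25.0%. The closed form for a block of 2m agrees: 2m/(m+1) = 6/4 = 1.5 certain allocations per block.
- Best guess: 4.1/6 = 68.3%, against 50% with no information.

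**Step 2: unfinished last blocks.** A stratum that stops partway through a block misses the later, most predictable positions.

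| Situation | Certain share |
|---|---|
| Stratum of 12 | 3.0/12 = 25.0% |
| Stratum of 11 | (1.5 + 0.10 + 0.40)/11 = 2.0/11 = 18.2% |
| Blocks within centre only, 24 patients | 6.0/24 = 25.0% |
| Blocks within centre only, 22 patients | (3 × 1.5 + 0.10)/22 = 4.6/22 = 20.9% |
| Two risk strata in a centre of 22 to 24, risk split assumed from 50:50 to 90:10 | about 20 to 21% |
| As above with strongly unequal centre sizes (assumed), mean 22.4 | about 21% |

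Over the whole trial, 0.20 × 2013 = 403 and 0.25 × 2013 = 503, so roughly 400 to 500 allocations.

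**Step 3: if blocks are not kept within centre.** A site does not see other sites' assignments, so it could determine essentially none.

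**Step 4: randomly varying lengths.** This was simulated in a stratum of 12. The observer is assumed to know the set of possible lengths but not their order, and to use all past assignments.

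| Scheme | Certain | Best-guess accuracy |
|---|---|---|
| Fixed 6 | 25% | 68% |
| 4, 6, 8 | about 2.4% | about 66.5% |
| 6, 8, 10 | about 2.2% | about 64% |

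In a stratum of 11, best-guess accuracy is about 65.4% with fixed 6, 65.4% with 4/6/8 and 64% with 6/8/10. The gain is therefore in removing certainty. Guessing in general improves by 0 to about 4 percentage points.

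**The case against.** A reader might infer that a quarter of allocations are predictable to the person who enrols patients. The protocol does not support that, for three reasons.

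- **Stratified blocking is inferred.** The text asks for balance by centre and by risk, but names neither strata nor separate lists. If blocks cross centres, the problem all but disappears. This stands as a condition on the finding. However, balance per centre would then have no stated mechanism, so within-centre blocking remains the natural reading.
- **A quarter is an upper bound at the planned sizes.** It is reached when strata fill in multiples of 6. This stands, and about a fifth is the better planning figure.
- **The enroller's knowledge is not established.** One investigator knows the allocation and collects intra-operative data, and another is blinded and scores outcomes. Who enrols is not said. Different anaesthetists may each see only their own cases. Prediction needs one person who knows the block length, follows every assignment in the stratum and influences enrolment. This stands, but nothing in the protocol prevents it.

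A reader might also infer that enrolment is in fact biased, for instance by staff who favour higher PEEP in obese patients. The introduction points both ways on preference. It argues that PEEP should in theory be higher in obese patients, yet reports that most patients in an observational study, obese ones included, received low or no PEEP. No motive is shown, and no effect on the primary endpoint can be estimated.

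Finally, the change would come partway through the trial. Data on 618 patients were already available when the sample size was re-estimated (section 6.4), so strata already filled gain nothing.

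**Conclusion.** The concern holds in conditional form. The protocol fixes and discloses one block length of 6 for an intervention that is open to at least one investigator per site. If blocks run within centre (and risk class), a site member who tracks earlier allocations could deduce with certainty up to a quarter of them before enrolment: 25% in complete blocks, about a fifth at planned centre and stratum sizes, and 18% in a stratum of 11.

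Three assumptions carry this: blocking is within centre, someone at the site follows every assignment in the stratum, and that person can influence who is enrolled. The first is the natural reading, and the other two are neither stated nor excluded. It is an avoidable weakness in concealment that should be mended because mending it is cheap. It is not shown bias.

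**What to change.** - For all blocks not yet opened, use randomly varying block lengths, for example 6, 8 and 10.
- Hold the lengths only in a restricted randomization specification, and delete the parenthesis giving the block length from the section on randomization arms.

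**Gain.** Certain allocations fall from 25% to about 2%. Best-guess accuracy falls only from about 68% to 64–65%, so the case for the change rests on certainty.

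**Cost.** New list segments on the existing website and one line of protocol text. Balance within small strata becomes slightly looser. Allocations already made are untouched. At most 2013 − 618 = 1395 patients would benefit, and fewer if recruitment had moved on or blocks were already open.
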